### Strategies to improve adherence to interventions

1) telephone follow-up; 2) weekly electronic counseling in order to improve patient's participation by reducing barriers such as geographical distance and time constraints; 3) husbands of the participant will also receive free dietary consulting to improve compliance and family support.

### Outcomes

The primary outcomes included gene expressions of IL-1α and 5α-reductase. The secondary outcomes consist serum levels of biochemical parameters comprising fasting blood sugar, fasting insulin, homeostasis model assessment of insulin resistance and quantitative insulin sensitivity check index, as well as serum androgen concentrations (testosterone, 5α-dihydrotestosterone) and anthropometric indices (height, weight, BMI, hip circumstance, waist circumstance, waist-hip ratio, waist-height ratio), body composition (muscle mass, fat mass, fat-free mass, and other factors such as trunk fat mass), physical activity, and dietary intake (energy and nutrient intake).

#### Demographic data and anthropometric measurements 

A form including: full address, age, gender, income, employment, ethnicity, level of education, and medical history (dose and type of medicine and supplements) will be completed for each participant.

Participant's weight, height, body circumferences (waist, hip), BMI, and waist-hip ratio as well as body composition analysis (fat mass, muscle mass, fat free mass) will be measured on the first and last day of the intervention. Weight will be measured to the nearest 0.5 kg (possible errors) using a pre-calibrated electronic scale (Seca, Germany). Height will be measured without shoes with an accuracy of 0.1 cm using a Seca wall stadiometer. Then BMI will be determined as weight (kg) divided by the square of their height (m²). Waist (cm) will be measured as the distance between the lowest rib and the iliac crest. Additionally, the hip circumference will be measured around the largest part of the hip. The waist-hip ratio will be the ratio of waist to hip circumference. The waist-height ratio will be measured by dividing the waist circumstance by the height. Body composition will be determined using body composition analyzer (Tanita BC-418, Tokyo, Japan), at the beginning of the study and after 12 wk of the study. All the measurements will be repeated by a trained assessor and recorded as average.

#### Biochemical measurements

After 2 wk of run-in period and considering 12-hr overnight fasting, 8 cc of blood samples will be collected in the morning from each participant, in the beginning, and at the end of the study.

5 cc of samples will be transferred to clot-activator tubes and then centrifuged for 30 min to separate the serum. Another 3 cc of blood samples will be collected in EDTA- coated tubes to seperate the plasma and buffy coat (the layer between red blood cells and plasma) and prepare buffy coat for gene expression assays. The allocated serum, plasma, and buffy coat will be stored immediately at -70 C. Before storage, the tripura isolation reagent will be added to the isolated buffy coat.

Serum levels of insulin, testosterone, and 5α-dihydrotestosterone will be evaluated using the enzyme-linked immunosorbent assay (ELIZA method), (ELISA kit, Monobind, California, United State). Fasting blood sugar will be measured by commercial kit using an enzymatic colorimetric method (Pars Azmoon, Tehran, Iran). Homeostasis model assessment of insulin resistance will be calculated, using the following formula: 

$$HOMA-IR=\frac{fastingbloodsugar\left(\frac{mg}{dl}\right)*Insulin}{450}$$

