### Statistical methods

The values of quantitative variables will be presented as the mean 
±
 standard deviation, and qualitative variables will be expressed as numbers and percentages. The normality of data will be examined by the Kolmogorov-Smirnov test.

The frequency among study groups will be compared using the Chi-square test. Independent sample *t* test and 2-way ANOVA will be applied to estimate the mean of quantitative variable changes and interactions between study groups; Bonferroni correction will be considered for multiple comparisons; and analysis of covariance (ANCOVA) will be used to compare the differences in the mean of quantitative data between the studied groups, while taking into account the influence of possible confounding variables. Before statistical analysis, all data will be checked for accuracy and completeness. All statistical analysis will be conducted using SPSS 22 (SPSS, Inc, Chicago, IL, USA). A p-value 
<
 0.05 will be defined as a statistically significant level.

The “intention-to-treat" and “per protocol analysis" approaches will be performed for data analysis. The “intention-to-treat" analysis considers all participants in their main randomized groups, regardless of whether they follow the prescribed intervention according to the protocol or not, and also ignores non-compliance and withdrawal. Per protocol analysis, which accurately reflects what has been done, will be conducted based on actual adherence to the interventions.

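### The printed HOMA-IR formula divides by 450 where the standard definition gives 405; applied as printed, it would make absolute HOMA-IR figures 10% too low, without changing any test result.

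*Protocol article*

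**What the plan says.** The Outcomes section of the protocol article lists HOMA-IR among the secondary outcomes, in the run "fasting insulin, homeostasis model assessment of insulin resistance and quantitative insulin sensitivity check index". The list does not rank these measures.

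The Biochemical measurements section fixes how the index is derived: "Homeostasis model assessment of insulin resistance will be calculated, using the following formula". The formula that follows multiplies fasting blood sugar by insulin and divides by 450. The glucose unit, mg/dl, is printed inside the formula; insulin carries no unit. No source or reason is given for 450, and no other section gives a different divisor.

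The Statistical methods section compares means and mean changes between groups by t test, two-way ANOVA and ANCOVA. It does not dichotomise HOMA-IR.

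**The concern.** Because the glucose unit is part of the formula, the divisor can be checked against the definition of the index, and 450 does not agree with it. This is a stated derivation rule for a named outcome, not a detail left to a fuller document. The formula is intact and legible, so damage in text extraction does not explain it.

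What is at stake is the absolute scale of HOMA-IR. If the rule is followed literally, the published means, changes and differences would be on a scale about one tenth smaller than that of studies using the standard index. Anyone who set those figures beside other studies, or pooled raw mean differences, without noticing the divisor would carry the error forward.

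**Working it through.** **Inputs**

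- Divisor as printed: 450 (Protocol article, Biochemical measurements).
- Glucose unit in the formula: mg/dl (same place). Insulin unit: not stated.
- Assumed: standard constant 22.5, for glucose in mmol/L and insulin in µU/mL. The article does not print it; it is the definition of the index.
- Assumed: 18.0 mg/dl of glucose per mmol/L (range 18.0 to 18.02). The article does not print it; it is a unit conversion.

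**Step 1: can 450 be reproduced?**

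Divisor for glucose in mg/dl = 22.5 × (mg/dl per mmol/L).

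- With 18.0: 22.5 × 18.0 = 405.0.
- With 18.016: 22.5 × 18.016 = 405.4.

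So 450 is not reproduced. To obtain it, one of the two constants would have to change:

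- conversion factor = 450 / 22.5 = 20.0 mg/dl per mmol/L, or
- index constant = 450 / 18.0 = 25.0.

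Neither is the standard value.

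**Step 2: could a different insulin unit explain it?**

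With insulin in pmol/L, the divisor would be 405 × 6.0 = 2430 or 405 × 6.945 ≈ 2813, depending on the conversion used. Neither is near 450. Since 450 and 405 share the same digits, a transposition is the likeliest explanation.

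**Step 3: size of the effect**

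Printed / standard = (G × I / 450) / (G × I / 405) = 405 / 450 = 0.90, whatever the glucose G and insulin I. The correction factor is 450 / 405 = 1.111.

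Illustration with chosen values of 90 mg/dl and 10 µU/mL:

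- as printed: 90 × 10 / 450 = 2.00
- standard, in mg/dl: 90 × 10 / 405 = 2.22
- cross-check in mmol/L: 90 / 18 = 5.0, and 5.0 × 10 / 22.5 = 2.22

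**Step 4: what changes and what does not**

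Multiplying every observation by the same constant multiplies means, standard deviations, standard errors, absolute changes, absolute differences and confidence limits by that constant. It cancels from test statistics, ratios and standardised effects. A simulated pair of arms with 24 women each showed this:

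| Quantity | Divisor 450 | Divisor 405 |
|---|---|---|
| Difference in means | 0.654 | 0.727 |
| t statistic | 2.81 | 2.81 |
| p-value | 0.0073 | 0.0073 |
| Ratio of means | 1.331 | 1.331 |
| Difference in log means | 0.348 | 0.348 |

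Only the absolute difference moves, and 0.654 / 0.727 = 0.90.

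**The case against.** The strongest reply is that this is harmless. The factor is identical in all four arms and at both visits, so no between-arm test or conclusion in this trial is altered. HOMA-IR is one of many secondary outcomes. The primary outcomes are gene expressions, and fasting sugar, insulin and QUICKI do not pass through this formula. The Eligibility criteria and the randomisation strata do not use HOMA-IR, and the Sample size section does not name it. The divisor may be no more than a misprint that never reaches the analysis syntax. Even if it does, the formula is published, glucose and insulin are both measured, and the index can be rescaled or recomputed at any time. All of this stands, and it sets the weight of the point. It does not make the printed formula right.

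It is also fair to object that 22.5 and 18 come from outside the article, and that the exact 10% takes insulin to be in µU/mL. That is why both are listed as assumptions. The missing insulin unit is not a separate defect, since a condensed article may leave assay units to the full protocol.

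Four stronger readings are tempting, and the article does not support them:

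- **HOMA-IR is the trial's main measure of insulin resistance.** The Outcomes section lists "homeostasis model assessment of insulin resistance and quantitative insulin sensitivity check index" side by side, without ranking them.
- **The results could not be compared or pooled with other studies.** Only unadjusted comparison, or pooling of raw means, is affected; multiplying by 1.111 restores the standard scale.
- **Women would be misclassified as not insulin resistant.** The protocol states no cut-off and plans no such classification.
- **Reported values are already wrong.** The article describes a calculation still to be done.

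**Conclusion.** The divisor is wrong as printed, given the standard definition of the index and 18 mg/dl per mmol/L; it should be 405. The consequence is conditional. If, and only if, the formula is applied as printed, absolute HOMA-IR figures will be 0.90 of their size on the standard scale, with insulin in µU/mL. No inference in the trial depends on it, and the error is fully reversible. It is a minor correction, worth making because it concerns the definition of a named outcome and costs almost nothing.

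**What to change.** - In the protocol, replace 450 with 405 in the HOMA-IR formula, and state that glucose is in mg/dl and insulin in µU/mL.
- Check that the analysis syntax divides by 405.
- If any HOMA-IR values have already been derived with 450, recompute them from the stored glucose and insulin, or multiply by 450/405 = 1.111.

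The cost is one constant and one unit in the text, plus a check of the syntax. No new measurements are needed, and the sample size, randomisation and planned tests are unaffected.

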#### Gene expression assay

According to the kit protocol (Favorgen Biotech Corp., Taiwan), the buffy coat fraction of whole blood cells will be used for total RNA extraction. RNA concentration will be analyzed using spectrophotometer (DS-11, DeNovix) at 260 nm. Purity will be considered as an A260/A280 ratio of about 2 (24). cDNA will be synthesized from high-quality mRNA using a cDNA synthesis kit (GeneAll Biotechnology Co.). Forward and reverse primers are selected after reviewing previous studies (25-27) and checked by primer designing tools (Primer Blast, OLIGO 7 primer analysis software), as shown in table I.

IL-1α and 5α-reductase expression levels will be assessed by SYBR-green real-time PCR detection method using the kit protocol (Yekta Tajhiz Azma, IRAN), and the StepOne real-time PCR system (Applied Biosystems, Foster City, California, USA). GAPDH (glyceraldehyde phosphate dehydrogenase) will be chosen as the housekeeping gene.

**Table 1 T1:** Real-time PCR primer sequences

**Gene**	**Forward**	**Reverse**
**5α-reductase **	TGGCGCTTCTCTATGGACTT	GGAAGCAACACTGCAGTTGA
**Interleukin 1 alpha **	ACTGCCCAAGATGAAGACCA	TTAGTGCCGTGAGTTTCCCA
* **GAPDH ** * **(Reference gene)**	CAAGAGCACAAGAGGAAGAGAGAG	TCTACATGGCAACTGTGAGGA
*GAPDH:* Glyceraldehyde-3-phosphate dehydrogenase, PCR: Polymerase chain reaction		

#### Dietary intake

Food consumption information will be obtained through 3-day dietary records including 2 days per week and one weekend. Before the study, participants will be given adequate training on food consumption and will be provided with a guide including written examples for completing a questionnaire that simply explains how to accurately record food. The participants will be taught to use standard kitchen measuring tools to accurately determine the portion size. To reduce memory errors, they will be asked to make a detailed list of foods and beverages exactly when eating. The expert dietitian will review the completed dietary records, ingredient lists, and preparation methods, while will be blind to the study allocation. Each daily food record will be calculated by the Nutritionist IV software.

#### Physical activity

The metabolic equivalent of task-hours (MET-h)/day will be applied to assess physical activity questionnaire data (28).

### Sample size

The sample size of 24 in each group was determined according to α = 0.05, the power of 80%, dropout rate of 20%, and considering a minimal clinically important difference of 0.969 and an effect size of 1, based on Heshmati et al. study (21) using the following formula: 

$$n=\frac{{\left(Z_{1-\alpha /2}+Z_{1-\beta }\right)}^{2}\left(S_{1}^{2}+S_{2}^{2}\right)}{{\left(\mu_{1}-\mu_{2}\right)}^{2}}$$

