The dietary approaches to stop hypertension (DASH) diet has been suggested as an effective treatment option (12). DASH diet, as a low-glycemic diet (13), with a high concentration of antioxidants, can have beneficial effects in reducing insulin resistance (14), inflammation (15), and free androgen index (16). This diet is rich in vegetables, low-fat dairy products, fruits, whole grains, poultry, fish, and nuts, but is limited in foods high in sodium, cholesterol, saturated fat, red and processed meat, refined grains, sweets, and sugary drinks (12). In the last decade, the antioxidative effects of plant polyphenols have been considered (17). Indeed, among natural phenols, the therapeutic properties of curcumin have been further investigated (18). Curcumin (diferuloylmethane) is a lipophilic yellow pigment extracted from turmeric rhizomes (*Curcuma longa L.*) (19). Curcumin supplementation improves glycemic control and lipid metabolism, and reduces radical oxygen species in PCOS patients (20, 21).

The anti-inflammatory and antioxidant benefits of both the DASH diet and curcumin have been demonstrated by meta-analysis results (15, 22). Therefore, we plan to investigate the effect of the DASH diet in combination with curcumin supplements on *IL-1
α

* and *5
α

* reductase gene expressions and improvement of insulin resistance and hyperandrogenism.

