### Study strengths and limitations

This will be the first study to investigate the effects of the DASH diet or curcumin supplementation on *IL-1
α

* gene expression in human. This study will be the first clinical trial that investigates the co-administration of the DASH diet and curcumin supplementation in patients with PCOS. The frequency of PCOS women with BMI: 18.5-25 is probably low, which could increase study time and lead to bias in results.

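### The 24 per group does not follow from the printed formula and inputs, which give 20 with dropout, and the 0.969 behind it has no stated outcome, unit or SD

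*Protocol article*

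**What the plan says.** The Sample size section opens "The sample size of 24 in each group was determined according to α = 0.05" and continues with "the power of 80%, dropout rate of 20%, and considering a minimal clinically important difference of 0.969 and an effect size of 1". It says the figures are based on reference 21 and prints the two-sided formula for comparing two independent means. It gives no SD and does not name the variable that 0.969 refers to. The Abstract gives the total as 96 in four equal groups, which agrees with 4 × 24.

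The Outcomes section names two primary outcomes, the gene expressions of IL-1α and 5α-reductase. The Introduction cites references 20 and 21 for this statement: "Curcumin supplementation improves glycemic control and lipid metabolism, and reduces radical oxygen species in PCOS patients". Under Study strengths and limitations, the article says of IL-1α gene expression in humans: "This will be the first study to investigate the effects of the DASH diet or curcumin supplementation on" it.

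**The concern.** The section prints a formula, its inputs and its result, so a reader can check it, and the three do not agree. This is not detail that a condensed article leaves to a fuller document.

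The 80% power claim is also not attached to a primary outcome. The target difference is called clinically important, yet its variable and scale are not given, and the source is cited elsewhere in the article for other kinds of outcome. At stake is whether a reader can tell what difference in IL-1α or 5α-reductase expression the trial is sized to detect, and whether 24 per group is generous or only just enough. That depends on the unstated basis.

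**Working it through.** **Inputs, all from the Sample size section:** α = 0.05, two-sided (the formula uses Z at 1−α/2); power 80%; dropout 20%; difference 0.969; effect size 1. If effect size means difference divided by SD, the implied SD is 0.969, but that is a deduction, as the section states no SD.

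**The plan's own formula at effect size 1.** With equal SDs, n = 2(Z₀.₉₇₅ + Z₀.₈₀)² / d² = 2 × (1.960 + 0.8416)² / 1² = 15.70, so 16 evaluable. Allowing for dropout, 16 / 0.8 = 20. The cruder 16 × 1.2 = 19.2 also rounds up to 20. The total is 4 × 20 = 80. The stated 24 and 96 are not reproduced.

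**Other readings at the stated α and power:**

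| Reading | Evaluable per group | After dividing by 0.8 | Total |
|---|---|---|---|
| Printed formula, d = 1 | 15.70 → 16 | 20 | 80 |
| Printed formula, difference 0.969, SD 1 (assumed) | 16.72 → 17 | 21.25 → 22 | 88 |
| t-test, d = 1 | 16.71 → 17 | 21.25 → 22 | 88 |
| t-test, d = 0.969 | 17.73 → 18 | 22.5 → 23 | 92 |

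The range is 20 to 23 per group, and no row gives 24.

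**Routes that do reach 24, each needing something the section does not state:**
- Dropout applied twice: 16 / 0.8 = 20, then 20 × 1.2 = 24.
- A t-test with an effect size that rounds to 1: d = 0.95 gives 18.41 → 19, and 19 / 0.8 = 23.75 → 24.
- A 15% rank-test allowance on the t-test size: 16.71 × 1.15 = 19.22 → 20, then 20 × 1.2 = 24.
- One-sided 0.05 with 90% power at d = 0.969: 18.24 → 19, and 19 / 0.8 = 23.75 → 24.
- α = 0.025 for each of two primary outcomes: 2 × (2.2414 + 0.8416)² = 19.01, and 19.01 / 0.8 = 23.8 → 24. Rounding first gives 20, then 25.

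**What 24 per group delivers.** After 20% dropout, 24 × 0.8 = 19.2, so about 19 evaluable. For one two-group comparison by t-test:
- α = 0.05, d = 1: 85% power with 19 per group and 92% with 24.
- α = 0.05, 80% power, 19 per group: detectable difference about 0.93 SD (about 0.91 by normal approximation).
- α = 0.025, d = 1, 19 per group: 77% power. Reaching 80% would need 20.3 → 21 evaluable, and 21 / 0.8 = 26.25 → 27 enrolled.

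**The source of 0.969.** Reference 21 is cited in the Introduction for curcumin in PCOS patients. The limitations section says no earlier human study has examined curcumin or the DASH diet on IL-1α gene expression. If both statements are right, 0.969 does not appear to be an IL-1α expression difference taken from reference 21. The article makes no such claim to be first for 5α-reductase.

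**The case against.** The strongest reply is that nothing is at risk. Twenty-four exceeds 20, so for a single two-group comparison at 1 SD the trial has more than its stated power, and recruitment need not change. On the less literal readings the gap is only one or two per group. The effect size is printed as 1 without decimals, and the Statistical methods section names the independent t-test. A t-test calculation at about 0.95 SD would give exactly 24. All of this stands. It limits the importance of the point and shows that the sponsor's route may have been sensible. It does not make the printed formula and inputs yield 24.

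Two stronger readings are tempting.

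- A reader might infer that α was really split to 0.025 for the two primary outcomes, since 19.01 / 0.8 lands on 24. The documents do not support this. The section says 0.05, the Statistical methods section uses 0.05 and mentions Bonferroni only for multiple comparisons, and several other unstated routes also reach 24. Under the planned t-test, a 0.025 level would need 27 per group.
- A reader might infer that 0.969 cannot belong to any primary outcome. That goes too far. The claim to be first concerns IL-1α only, so 5α-reductase remains open. Basing a figure on a study also leaves room for using another variable as a planning surrogate. Reference 21 is not at hand to settle it.

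**Conclusion.** The stated size is wrong as written: 20 per group (80 in total) by the printed formula, and 20 to 23 across readings at the stated α and power, against 24 (96). The gap is 4 per group on the literal reading and 1 to 4 across readings. The basis of 0.969 cannot be traced, and it does not appear to be an IL-1α expression difference from the cited study.

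This is an error of reporting and traceability, not of too few patients. It would be wrong to infer that the trial is underpowered: about 85% power remains with 19 evaluable per group. That figure assumes one unadjusted two-group t-test, a true difference of 1 SD, α = 0.05 and 20% dropout. If the two primary outcomes share α, it falls to about 77%, which is why the basis should be disclosed. The paragraph should be corrected, but the discrepancy does not threaten the trial's conclusion.

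**What to change.** Keep 96 and rewrite the Sample size paragraph so that it reproduces, in one of two ways:

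1. State the calculation actually used, including any α adjustment, extra allowance, unrounded effect size or t-test basis that leads to 24.
2. If that cannot be recovered, state what 96 delivers: 24 enrolled and about 19 evaluable per group; about 85% power by t-test at 1 SD for one unadjusted two-group comparison at α = 0.05; a detectable difference of about 0.93 SD at 80% power; and about 77% power at 1 SD if the two primary outcomes share α at 0.025 each.

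In either case, name the variable, unit and SD behind 0.969, and state 1 SD as a planning assumption for IL-1α and for 5α-reductase expression. An α = 0.025 rationale should be written in only if it was the one used. The cost is one reworded paragraph, with no added patients and no change to the conduct of the trial.
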